## **8 Study Assessments and Procedures**

Study procedures and their timing are summarised in the SoA (Table 1-1 for Part 1 and Table 1-2 for Part 2). Protocol waivers or exemptions are not allowed.

Adherence to the study design requirements, including those specified in the SoA, is essential and required for study conduct.

All screening evaluations must be completed and reviewed to confirm that potential subjects meet all eligibility criteria. The Investigator will maintain a screening log to record details of all subjects screened and to confirm eligibility or record reasons for screening failure, as applicable.

Procedures conducted as part of the subject's routine clinical management (e.g., blood count) and obtained before signing of the ICF may be utilised for screening or baseline purposes provided the procedures met the protocol-specified criteria and were performed within the time frame defined in the SoA.

The maximum amount of blood collected from each subject over the duration of the study, including any extra assessments that may be required per protocol, will not exceed 500 mL.

Repeat or unscheduled samples may be taken for safety reasons or for technical issues with the samples.

### **Informed Consent**

Informed consent must be documented, according to Appendix 1, Section 10.1.3.

### **Eligibility Criteria**

All inclusion and exclusion criteria will be reviewed by the Investigator or designee to ensure that the subject qualifies for the study.

### **Medical History**

A medical history will be obtained by the Investigator or qualified designee. The medical history will collect all active conditions and any prior condition that the Investigator considers to be clinically relevant, including previous SARS-CoV-2 infection(s).

## **Current COVID-19 History**

Details regarding COVID-19 signs and symptoms with date of onset and stop date or ongoing will be collected.

The confirmation of the current SARS-CoV-2 infection by positive RT-PCR test and/or positive antigen test, will be captured.

The presence of anti-SARS-CoV-2 antibodies in blood samples will be determined at baseline by a central laboratory.

## **Prior and Concomitant Medications Review**

The Investigator or qualified designee will review prior medication use and record prior medications taken by the subject within 30 days prior to screening. COVID-19 vaccination details will be recorded without limitation in time.

The Investigator or qualified designee will record medication, if any, taken by the subject during the study through the last visit. Concomitant medications will be recorded throughout the full duration of the study (or longer if related to an SAE).

## **8.1 Efficacy Assessments**

### **8.1.1 Clinical Status According to 8-point Ordinal Scale**

The clinical status will be assessed at the timepoints specified in the SoA (Table 1-1 for Part 1 and Table 1-2 for Part 2), using an 8-point ordinal scale (see Appendix 2), previously used in Study NCT04280705 (Beigel et al 2020).

Recovery will be defined as achieving a clinical status  $\leq 3$  on the 8-point ordinal scale. This will be considered 'sustained recovery' if the clinical status remains  $\leq 3$  for the subsequent 14 consecutive days. Time to sustained recovery will be defined as the time between treatment administration and the first occurrence of recovery which is subsequently shown to be sustained..

Deterioration in the clinical condition of the subject such that intensive care is required will be considered a treatment failure and the end of study visit should be performed.

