| 
Primary
 
To evaluate the efficacy of a single intravenous XVR011 infusion in subjects hospitalised for COVID-19, compared to placebo
           | 
 
Time to sustained recovery (i.e., clinical status reaching level 1 to 3 of the 8-point ordinal scale) within 28-day FU period; where recovery must be confirmed to be maintained at level 3 or lower for 14 consecutive days
 
                                                                                                                                                                                                                                                                                                                                                                                                                                                                                                                                                                                                                                                                              |
| 
Secondary
 
To further evaluate the efficacy of a single intravenous XVR011 infusion in subjects hospitalised for COVID-19, compared to placebo
 | 
 
Proportion of subjects who are alive and do not require any form of mechanical ventilation a at Day 8
 
Proportion of subjects requiring any form of mechanical ventilation a within 28-day FU period
 
Proportion of subjects requiring ICU transfer within 28-day FU period
 
Time to sustained hospital discharge (i.e. discharge with no re-hospitalisation after initial discharge for treatment of COVID-19 related events in the following 14 days) within the 90 day FU period
 
Total duration of oxygen supplementation within 28-day FU period
 
Proportion of subjects with clinical status evolving to each level of the 8-point ordinal scale at Days 2, 3, 4, 8, 15, 22 and Day 29, compared to baseline
 
Proportion of subjects with COVID-19 related symptoms
 
All-cause mortality rate within 28-day FU period
 
 |

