### **7.2 Subject Discontinuation/Withdrawal from the Study**

A subject may withdraw from the study at any time at his/her own request or may be withdrawn at any time at the discretion of the Investigator for safety, behavioural, or administrative reasons. The subject will be definitively discontinued from both the study treatment and the study at that time.

If the subject withdraws consent for disclosure of future information, the Sponsor may retain and continue to use any data collected before such a withdrawal of consent.

If a subject withdraws from the study, he/she may request the destruction of any samples taken and not tested, and the Investigator must document this in the site study records.

At the time of discontinuing from the study, if possible, an early discontinuation (ED) visit should be conducted, as shown in the SoA. Refer to the SoA for data to be collected at the time of study discontinuation and follow-up and for any further evaluations that need to be completed.

When a subject participation has been terminated prior to completing the study, the reason is recorded as follows:

- Pregnancy
- Adverse event
- Treatment failure
- Protocol violation
- Lost to follow-up
- Subject withdrew consent at own request
- Other

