#### **8.3.1 Time Period and Frequency for Collecting AE and SAE Information**

All AEs and SAEs will be collected from the signing of ICF to the EOS visit at the timepoints specified in the SoA (Table 1-1 for Part 1 and Table 1-2 for Part 2).

All SAEs will be recorded and reported to the Sponsor or designee within 24 hours, as indicated in Appendix 4. The Investigator will submit any updated SAE data to the Sponsor within 24 hours of it being available.

Investigators are not obliged to actively seek AEs or SAEs after the conclusion of study participation. However, if the Investigator learns of any SAE, including death, at any time after a subject has been discharged from the study, and he/she considers the event to be reasonably related to the study treatment or study participation, the Investigator must promptly notify the Medical Monitor (or the Sponsor after study closure).

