### **9.4.1 General Considerations**

All statistical analyses will be performed by Parexel. All statistical analysis will be performed using the latest available version of SAS® (SAS Institute Inc., Cary, North Carolina, United States of America [USA]), version 9.2 or higher.

Continuous data will be summarised by treatment group using descriptive statistics (number, mean, median, standard deviation [SD], minimum, and maximum). Categorical data will be summarised by treatment group using frequency tables (frequency and percent).

Unless other way specified, baseline will be taken as the last available assessment prior to dosing on Day 1.

All statistical tests will be 2-sided and will be performed at the 5% level of significance, thus 95% confidence intervals (CIs) will be computed, unless otherwise stated.

A protocol deviation is defined as any change, divergence, or departure from the study design or procedures of a study protocol. Protocol deviations can lead to the exclusion of a subject from the PPS. Protocol deviations will be reviewed and classified at the Blinded Data Review Meeting (BDRM) prior to unblinding; the exclusion of subjects from PPS will be decided at BDRM.

Unless otherwise stated, missing data will not be imputed.

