### **9.4.2 Primary Efficacy Endpoint**

For Part 1, refer to the safety analyses in Section 9.4.4.

For Part 2, the primary analysis for the primary endpoint (i.e., time to sustained recovery within the 28-day FU period) will be tested using the stratified (stratification factors used at randomisation) log-rank test in the FAS (if applicable) for the comparison of the 2 treatment arms. Kaplan-Meier curves will be presented, and median time to recovery and 95% CI will be calculated based on the Kaplan-Meier estimates. The Bayesian piecewise exponential model (Ibrahim et al 2001) will be used to calculate the time variant hazard ratios and 95% CI's. In this model, the stratification factors at the time of randomisation (if applicable) will be used as covariates. In these subjects with mild to moderate COVID-19 disease, no mortality or small mortality rate is

anticipated; in case of death events, a censoring time will be imputed to handle deaths similarly to cases of no recovery by Day 29.

Further details on the methodology applied for the statistical analysis will be described in the protocol and statistical analysis plan (SAP).

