### 9.4.3 Secondary Efficacy Endpoints

Proportion of subjects who are alive and do not require any form of mechanical ventilation at Day 8. Proportion of subjects requiring non-invasive or invasive, mechanical ventilation, proportion of subjects requiring intensive care unit (ICU) transfer, and all-cause mortality rate within 28-day FU period will be presented.

Total duration (days) of oxygen supplementation within 28-day FU period, change from baseline in the nasopharyngeal viral load (RT-qPCR) will be reported as continuous endpoints.

Proportion of subjects with clinical status evolving to each level of the 8-point ordinal scale at Days 2, 3, 4, 8, 15, 22, and Day 29, compared to baseline, will be tabulated in a shift table.

Time to event secondary endpoints will be analysed using a methodology similar to the analysis of the primary efficacy endpoint.

In Part 1, the secondary endpoints will be summarised descriptively.

In Part 2, the comparison between XVR011 and placebo will be conducted for every secondary endpoint and resulting p-values will be presented.

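### Need for intensive care triggers the end-of-study visit, which cuts off the 28-day endpoints in the sickest subjects; any bias in the primary endpoint is conditional

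*Protocol*

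**What the plan says.** Section 8.1.1 of the protocol provides that, if a subject deteriorates so that "intensive care is required will be considered a treatment failure and the end of study visit should be performed". Section 7.2 states: "When a subject participation has been terminated prior to completing the study, the reason is recorded as follows"; treatment failure is on the list that follows. Section 8.3.1 sets the safety window: "All AEs and SAEs will be collected from the signing of ICF to the EOS visit". It adds that investigators need not actively look for events once participation is over. No section says that follow-up continues after an EOS visit triggered by intensive care.

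The Part 2 endpoints in Table 3–2 run over the whole 28-day follow-up. They include "All-cause mortality rate within 28-day FU period", ordinal status at visits to Day 29, total oxygen duration, any mechanical ventilation, ICU transfer and the safety proportions. The ordinal scale in Section 10.2 has level 7 for invasive ventilation or ECMO and level 8 for death.

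The primary endpoint is time to recovery, "where recovery must be confirmed to be maintained at level 3 or lower for 14 consecutive days". Section 9.4.2 gives one rule for subjects who cannot recover: "in case of death events, a censoring time will be imputed to handle deaths similarly to cases of no recovery by Day 29". It says nothing on ICU exits and refers further method to the SAP. Section 9.4.1 adds: "Unless otherwise stated, missing data will not be imputed".

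**The concern.** Study treatment is one infusion on Day 1, so by the time a subject needs intensive care there is normally no study treatment left to stop. The rule therefore mainly ends observation. It does so at the point after which invasive ventilation, ECMO and death are most likely, and those states are part of the endpoints. An SAP can choose how to analyse data but cannot recover data that sites were told not to collect.

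It is also unclear which assessments such a subject receives. In Part 2 the EOS visit is the Day 90 column of Table 1–2, with a separate early-discontinuation column. Section 7.2 calls for the early-discontinuation visit on leaving the study, while Section 8.1.1 calls for the end-of-study visit.

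The second issue is the primary analysis. If an ICU exit were censored on the day of exit, the Kaplan-Meier and log-rank methods would treat that subject as having the same recovery prospects as those still under observation. That is implausible, and the arm with more ICU transfers would appear to recover better.

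**Working it through.** **Endpoints set against the exit rule**

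- All-cause mortality to 28 days: truncated at exit. Section 8.3.3 follows SAEs already reported until resolution or stabilisation, which catches some later deaths. Section 10.4.2 says that an event outside the AE definition cannot be an SAE, and gives death from disease progression as an example. SAE follow-up is therefore not a vital-status safeguard.
- Ordinal status to Day 29: truncated, chiefly at levels 7 and 8.
- "Total duration (days) of oxygen supplementation within 28-day FU period": truncated at exit.
- Safety proportions to 28 days: new AEs after the EOS visit are not actively sought.
- ICU transfer: unharmed, because the event precedes the exit.
- Any mechanical ventilation: the footnote to Table 3–2 includes high-flow oxygen and CPAP. Only subjects on none of these, nor on invasive ventilation, at exit can be missed.

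**Number of subjects.** Section 2.1 gives 30% critical-care admission among hospitalised patients, but as general background. No rate for this population is in the documents, so a range is assumed. Of 408 subjects: 408 × 0.05 = 20, 408 × 0.10 = 41, 408 × 0.20 = 82 and 408 × 0.30 = 122 exits. If 20–40% of them die by Day 29 (also an assumption), 4–8, 8–16, 16–33 or 24–49 deaths fall after the exit visit.

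**Reproducing the plan's figures (Section 9.2, Table 9–1).** Not recovered at Days 5, 7 and 29: placebo 80%, 50%, 20%; XVR011 50%, 25%, 20%.

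- Interval hazard ratio = ln(XVR011 survival ratio) / ln(placebo survival ratio).
- To Day 5: ln 0.50 / ln 0.80 = 3.11.
- Days 5–7: ln(0.25/0.50) / ln(0.50/0.80) = 1.47.
- Days 7–29: ln(0.20/0.25) / ln(0.20/0.50) = 0.24.
- Events: 408 × 0.85 × 0.80 = 277, against 275 stated.

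The hazard ratios match and the events agree within 1%. Simulated log-rank power on these curves is about 84% with 347 evaluable subjects (408 × 0.85, split 231:116). It is 90–93% with 408 randomised under other drop-out handling. Both exceed the stated 80%; nothing below depends on that gap.

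**What censoring at exit does to the recovery estimate.** Suppose true recovery by Day 29 is 80%, and ICU subjects come from the 20% not recovered and exit at Day 5.

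- Placebo curve, 10% exits: after Day 5, 80 − 10 = 70 per 100 remain at risk and 60 recover. The estimate of no recovery is 0.80 × 10/70 = 0.114, so recovery reads 89%.
- XVR011 curve, 10% exits: 50 − 10 = 40 remain and 30 recover; 0.50 × 10/40 = 0.125, so recovery reads 88%.
- With 5% exits the same steps give 84% (0.80 × 15/75 = 0.16) and 83% (0.50 × 15/45 = 0.167).

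**Effect on the test.** Simulation on the Table 9–1 model; ICU subjects drawn from the 20% not recovered; exit within about the first week after dosing; unstratified log-rank test. ICU rates are XVR011 vs placebo.

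| Assumed ICU rates | Two-sided rejection, equal recovery, censored at exit | Power on Table 9–1 curves, censored at exit | Power, kept to Day 29 |
|---|---|---|---|
| 10% vs 10% | 3.8% | 98% | 92% |
| 5% vs 10% | 13% | 89% | 92% |
| 10% vs 20% | 63% | 81% | 93% |
| 5% vs 20% | 87% | 46% | 93% |
| 5% vs 15% (347 evaluable) | about 40% | about 60% | about 84% |

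The first four rows use 408 subjects with 15% exponential drop-out; the last uses 231:116. Wherever the ICU rates differ in this table, the error under equal recovery runs against XVR011. If the imbalance is reversed, one-sided false success for XVR011 is 12% at 10% vs 5% and 75% at 20% vs 10%, against a nominal 2.5%. With ICU subjects kept at risk to Day 29 as not recovered, two-sided rejection under equal recovery is 4.7–5.2% in the 408-subject scenarios and about 5% at 5% vs 15%.

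**The case against.** A reader might infer that the primary result is biased as the plan stands. The documents do not support that. No section says that ICU exits are censored at transfer. Treatment failure reads at least as naturally as non-recovery, Section 9.4.2 already has a category for subjects not recovered by Day 29, and the no-imputation sentence is a default. Censoring rules are commonly set in the SAP. This part of the objection stands, and the primary-endpoint bias is therefore put as conditional.

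The assumptions are also on the harsh side. Every ICU subject is placed among the 20% who never recover; at a 20% ICU rate that means all of them. Eligibility excludes high-flow oxygen, respiratory rate of 30 or more and neutrophil-to-lymphocyte ratio above 4, and Section 9.4.2 expects little or no mortality, so low ICU rates are plausible. ICU exits may also fall within the planned 15% drop-out rather than on top of it. At 5% vs 10%, power hardly moves.

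A reader might also infer that the ventilation endpoint is lost, or that nothing is known after exit. Neither follows. Many subjects will already have met the ventilation endpoint, and updates to SAEs already reported continue under Sections 8.3.3 and 10.4.3.

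Finally, death shortens oxygen duration with or without the ICU rule. How to handle that is a separate analysis choice and is not part of this point.

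What the objection leaves intact is the conflict between the exit rule and the 28-day mortality, ordinal-status, oxygen and safety endpoints.

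**Conclusion.** The contradiction is in the current text and does not depend on any assumed rate: Sections 7.2, 8.1.1 and 8.3.1 together end observation before Day 29 in subjects for whom Table 3–2 requires 28 days of data. Each 5% of subjects needing intensive care is about 20 of 408 with truncated mortality, ordinal, oxygen and safety data.

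The primary test is distorted only if these subjects are censored at exit. With equal ICU rates its false-rejection rate stays near nominal. With unequal rates, two-sided rejection under equal recovery was 13% to 87% in the scenarios examined. Power ranged from 89% (5% vs 10%) to 46% (5% vs 20%), both against 90–93% without that censoring. These figures rest on assumed ICU rates, exit in about the first week and ICU subjects who do not recover. Carrying them to Day 29 protects the log-rank error rate but would miss any later recovery and does not restore the other endpoints.

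**What to change.** Reconcile Sections 7.2, 8.1.1 and 8.3.1 with the 28-day endpoints by separating treatment failure as an outcome from the end of data collection:

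- In Section 8.1.1, remove the trigger for the end-of-study visit and record need for intensive care as an outcome.
- Continue clinical status, respiratory support, AE/SAE and vital-status collection to Day 29 (Part 2: Day 90), from hospital records where needed.
- Align Sections 7.2 and 8.3.1, so that treatment failure is not by itself a reason to terminate participation or to stop safety collection.
- In Section 9.4.2, state that ICU or treatment-failure subjects without observed sustained recovery stay at risk as not recovered to Day 29, as deaths do.

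This concerns data collection and analysis only; it says nothing on clinical care. The cost is amendment wording and record-based follow-up of a minority of subjects. No additional subjects are needed.

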### **8.1.2 Respiratory Parameters**

Oxygen supplementation details, respiratory rate and oxygen saturation (on room air and with oxygen supplementation) will be assessed at the timepoints specified in the SoA (Table 1-1 for Part 1 and Table 1–2 for Part 2):

- All non-invasive and invasive oxygen supplementation, including all forms of mechanical ventilation will be reported. The following information will be collected: type, flow rate and start & stop dates.
- Respiratory rate will be measured as part of vital signs (see Section 8.2.2).
- Oxygen saturation will be measured using pulse oximetry measurements, in accordance with the site standard operating procedures, on a medical-grade medical device. Measurements will be taken with a probe on the fingertip or earlobe (keeping the same methodology throughout the study, if possible) and recorded as percent oxygenated haemoglobin.

### **8.1.3 Viral Load**

The antiviral activity of study treatments will be assessed by measuring the nasopharyngeal viral loads.

Nasopharyngeal swabs will be collected at the timepoints specified in the SoA (Table 1-1 for Part 1 and Table 1–2 for Part 2). Samples will be tested for the presence of SARS-CoV-2 using the SARS-CoV-2 RT-qPCR assay. Virologic assessments will include quantitative measures of viral RNA and will be conducted by a central laboratory. At baseline and on Day 8, the genotype of the SARS-CoV-2 virus will be determined.

### **8.1.4 COVID-19 Related Symptoms**

Fourteen key COVID-19-related symptoms will be rated by the subject at the timepoints specified in the SoA (Table 1-1 for Part 1 and Table 1–2 for Part 2), using a questionnaire administered by the Investigator or designee (see Appendix 3). The questionnaire will include 1 question per symptom. Each symptom will be rated from 0 (no symptoms) to 3 (severe or  $\geq 5$ /day for vomiting and diarrhoea), except sense of smell and taste rated from 0 (same as usual) to 2 (no sense of smell/taste).

## **8.2 Safety Assessments**

Planned timepoints for all safety assessments are provided in the SoA (Table 1-1 for Part 1 and Table 1–2 for Part 2).

### **8.2.1 Physical Examinations**

A complete physical examination (screening only) will include assessments of the cardiovascular, respiratory, musculoskeletal, lymphatic, and neurological systems as well as general appearance, skin, eyes, ears, nose, throat and extremities examinations. Height will be measured and recorded at screening only and weight will be measured and recorded at screening and EOS/ED visit.

A COVID-19 symptom targeted physical examination (all other visits) will be performed to evaluate for status of COVID-19 associated symptoms, focusing at a minimum on respiratory function. Other body systems will be examined depending upon subject's complaints/symptoms.

Investigators should pay special attention to clinical signs related to previous serious illnesses.

